### Randomization, allocation concealment, and blinding

2.8

The random allocation sequence will be generated by an independent researcher who will not be involved in patient enrollment or perioperative management. A computer-generated randomization list will be created using an online tool (Research Randomizer; https://www.randomizer.org), assigning subjects identification numbers from 1 to 58 in a 1:1 ratio (remimazolam:propofol) without replacement. Simple randomization will be applied. No stratification or fixed block sizes will be used to minimize predictability and ensure equal allocation probability.

Allocation concealment will be ensured using sequentially numbered, opaque, sealed envelopes prepared in advance by the independent anesthesiologist responsible for randomization. The envelopes will be securely stored and opened only at the time of anesthesia induction. Investigators responsible for patient enrollment and anesthesia management will not have access to the randomization sequence beforehand.

After confirming eligibility and obtaining informed consent, the independent anesthesiologist will open the next envelope immediately before induction and disclose the allocation. An operating-room anesthesia nurse will prepare the study drug according to the assigned group.

The study will be conducted in a single-blind design. Participants and surgeons will be blinded to group assignment, whereas anesthesia providers and the operating-room anesthesia nurse will not be blinded due to the practical requirements of drug preparation and infusion management. To preserve blinding, syringes containing the study drugs will be placed in syringe pumps covered with opaque panels, preventing visualization of drug appearance or pump settings. Although remimazolam and propofol differ in appearance (colorless vs. milky white) and pump dose range (1–2 vs. 2.5–3.5, respectively), these characteristics will be concealed from participants and surgeons. Both groups will receive anesthesia guided to an identical depth target (PSI 25–50) using standardized anesthetic protocols to ensure comparability aside from drug assignment.

Emergency unblinding will occur only when knowledge of group assignment is necessary for immediate clinical care. Situations that may warrant unblinding include suspected severe drug-related adverse reactions such as anaphylaxis, unexpected prolonged emergence requiring identification of the anesthetic agent, severe hemodynamic instability unresponsive to protocol-directed management, or a request from regulatory authorities or the institutional review board (IRB). In such cases, the attending anesthesiologist will initiate unblinding using the allocation record, and the time, date, reason, and personnel involved will be documented and reported to the IRB.

### Data collection

2.9

Preoperative variables, including demographic characteristics, comorbidities, baseline vital signs, and medication history, will be collected from the electronic medical record and confirmed with the patient.

Intraoperatively, data on remimazolam or propofol infusion rate, remifentanil effect-site concentration, vital signs, continuous hemodynamic parameters (MAP, CO, CI, and SVV), and ventilator settings will be continuously recorded and synchronized with time-stamped events. Real-time physiologic data will be captured via an RS232C cable connected to the Vital Recorder software and downloaded to secure study computers for analysis (Lee and Jung, 2018).

The attending anesthesiologists will be aware of group assignment and will titrate anesthetic infusions according to hemodynamic responses and depth of anesthesia, as measured by the PSI. They will also document designated time points (T0–T43) throughout anesthesia. All intraoperative physiologic data retrieved from the Vital Recorder will be anonymized and provided to a separate research investigator blinded to group allocation. This open-label, blinded-assessment approach ensures objective and unbiased data collection and analysis.

In the PACU, vital signs and pain scores will be recorded before and after analgesic administration, along with documentation of PONV and any medications administered for symptom management.

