### Outcomes

2.6

The primary outcome of the study will be the time-weighted average (TWA)-MAP measured throughout anesthesia using an arterial line connected to a FloTrac™ sensor (Edwards Lifesciences, Irvine, CA, United States). For each participant, TWA-MAP will be calculated as the integral of MAP over elapsed time divided by the total observation duration, using the trapezoidal method. Data will be collected at approximately 1-min intervals when available, and measurements identified as technical artifacts (e.g., arterial line flushing, signal disconnection, damping artifacts, or recording errors) based on inspection of the arterial pressure waveform and corresponding clinical records will be excluded following data quality assessment. The primary analysis will compare TWA-MAP between the remimazolam and propofol groups to test the hypothesis that remimazolam-based TIVA will maintain a ≥20% higher intraoperative MAP than propofol-based TIVA.

Secondary outcomes will include the cumulative intraoperative burden of hypertension and hypotension. Hypertensive burden will be quantified as the area under the curve above the hypertension threshold (SBP ≥140 mmHg or MAP ≥100 mmHg), expressed in mmHg·min using the trapezoidal method. Hypotensive burden will be quantified as the area under the curve below the hypotension threshold (SBP <90 mmHg or MAP <65 mmHg), also expressed in mmHg·min. Group comparisons will assess whether remimazolam-based TIVA differs from propofol-based TIVA in hypertensive and hypotensive burdens. The time frame for secondary outcomes will extend from the start of induction to exit from the operating room.

In addition, intraoperative adverse hemodynamic events, including hypotension, hypertension, bradycardia, and tachycardia, will be recorded. Preoperative data will include patient characteristics, such as height, weight, age, diagnosis, scheduled surgical procedure, medical history, preoperative medication use, and baseline vital signs. Intraoperative data will include the surgical procedure performed, anesthesia duration, operative duration, degree of head-down tilt, vasopressin administration for bleeding control, estimated blood loss, fluid administration, and remifentanil dosage. Postoperative data will include post-anesthesia care unit (PACU) stay duration, PACU vital signs, and administration of additional medications, such as antiemetics and analgesics.

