### Monitoring and interim analysis

2.12

A formal data monitoring committee (DMC) will not be established for this trial, as it is a single-center, investigator-initiated study with a relatively small sample size and short perioperative follow-up period. The safety profiles of remimazolam and propofol are well established, and both agents are routinely used in clinical practice; therefore, an independent DMC is not deemed necessary.

Interim safety oversight will be conducted by the principal investigator in collaboration with two independent senior anesthesiologists who are not involved in participant recruitment or intraoperative management. Adverse events and protocol adherence will be reviewed quarterly. Any serious adverse events will be reported immediately to the IRB and managed according to institutional policy.

No formal interim efficacy analyses are planned due to the limited sample size (n = 58) and short perioperative observation period. However, an interim review will be performed after the first 20 participants have completed the study, focusing on serious adverse events such as severe hypotension, bradycardia requiring intervention, or anaphylaxis.

No statistical stopping boundaries or alpha-spending procedures will be applied. The trial may be terminated early under the following circumstances: unexpected serious adverse events directly attributable to the study drug, safety concerns raised by the IRB, or administrative or feasibility issues such as inadequate recruitment or loss of drug supply.

Access to interim safety findings will be restricted to the monitoring team (principal investigator and independent anesthesiologists). Investigators involved in patient care, surgeons, and participants will remain blinded to group assignment during interim evaluations. The IRB will make final decisions regarding trial continuation, modification, or termination based on recommendations from the monitoring team.

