The strengths of the study include its randomized, prospective design, standardized anesthetic and surgical protocols, and continuous arterial waveform–based hemodynamic monitoring using the FloTrac™ system. These features are expected to enhance the internal validity and reliability of intraoperative blood pressure assessment. Although a double-blind design is not feasible in this anesthetic trial, the single-blind approach—in which anesthesiologists are aware of group allocation but data collection and analysis are performed by blinded investigators—is intended to minimize bias and preserve the integrity of outcome assessment. Another strength of the study is the selection of a remimazolam induction regimen that reflects contemporary clinical practice and current safety considerations. Remimazolam induction will be performed at 6 mg/kg/h, which is within the approved dosing range and lower than the maximum recommended induction rate of 12 mg/kg/h. This dosing strategy was chosen in consideration of emerging evidence suggesting that lower induction infusion rates may reduce the risk of adverse events while maintaining satisfactory anesthetic conditions (Lee and Kim, 2024).

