The study has several limitations. First, it will be conducted at a single secondary care hospital and will include only relatively healthy female patients undergoing elective gynecologic laparoscopic surgery. Therefore, the generalizability of the findings may be limited, particularly to populations with different demographic or clinical characteristics. Second, the relatively modest sample size, although determined based on an *a priori* power calculation for the primary outcome, may limit statistical power for secondary outcomes and exploratory analyses. Therefore, the findings should be interpreted with appropriate caution. Third, transient blood pressure artifacts related to surgical manipulation or device calibration cannot be entirely avoided; however, predefined data-cleaning criteria will be applied to mitigate their impact. Fourth, postoperative long-term outcomes will not be evaluated in this study. Finally, a limitation of this study is the difference in drug delivery methods between study groups. Remimazolam will be administered by continuous infusion because no externally validated PK/PD-linked target-controlled infusion model is currently available for routine clinical use, whereas propofol will be administered using a target-controlled infusion system. Although this approach reflects contemporary anesthetic practice and enhances the clinical applicability of the study design, differences in administration strategy could influence anesthetic exposure and hemodynamic responses. Future studies employing validated PK/PD-guided administration methods for remimazolam may allow more direct comparisons between anesthetic agents.

Despite these limitations, the study is expected to provide high-quality evidence regarding the differential hemodynamic effects of remimazolam and propofol during laparoscopic gynecologic surgery. The findings may help anesthesiologists optimize anesthetic drug selection and intraoperative blood pressure management strategies, enhancing hemodynamic stability and improving patient safety in minimally invasive surgery.

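### The protocol overstates blinding: providers who know the arm mark the time points, and nothing described keeps artifact review of the pressure trace blind to the drug

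*Protocol article*

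**What the plan says.** **The assurance.** Section 2.9 (Data collection) ends its account of blinding with "This open-label, blinded-assessment approach ensures objective and unbiased data collection and analysis". The Discussion, listing strengths, says that "data collection and analysis are performed by blinded investigators". Section 2.12 (Monitoring and interim analysis) says: "Investigators involved in patient care, surgeons, and participants will remain blinded to group assignment during interim evaluations".

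**Who knows the arm.** Section 2.8 blinds participants and surgeons and states that anesthesia providers and the operating-room nurse are not blinded. Section 2.9 repeats that the attending anesthesiologists know the assignment, and continues: "They will also document designated time points (T0–T43) throughout anesthesia".

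**What is recorded and handed over.** Section 2.9 lists "data on remimazolam or propofol infusion rate, remifentanil effect-site concentration, vital signs" among the data captured continuously and synchronized with time-stamped events, alongside MAP. The recorder's physiologic data are then anonymized and passed to a separate investigator, described as blinded to allocation.

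**How readings are removed.** Section 2.6 (Outcomes) gives examples of technical artifacts (flushing, disconnection, damping, recording errors). Measurements so identified "based on inspection of the arterial pressure waveform and corresponding clinical records will be excluded following data quality assessment". It does not say who makes the decision. The Discussion says that "predefined data-cleaning criteria will be applied to mitigate their impact".

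**What follows from removal.** Under section 2.11, up to 5% missing values are linearly interpolated. Above 5%, the participant leaves the per-protocol set, and no intention-to-treat analysis is planned.

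**The concern.** MAP is captured by machine, so its recording is largely safe from the observer. Deciding which readings count is not automatic. Because the providers know the arm, blind processing of the trace is the main protection left for the primary outcome and the burdens, and the protocol relies on it as a strength.

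Two things weaken that reliance. First, some statements about who is blinded cannot stand together. Second, the safeguard described for the artifact step, anonymizing, removes the patient's identity and does not in itself remove the allocation. A reviewer who sees an infusion-rate channel or an ordinary anesthesia record could learn the arm. Section 2.4 gives flumazenil in the remimazolam group only, so even that one entry would disclose it.

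At stake are small shifts in TWA-MAP and larger shifts in the hypotensive and hypertensive burdens, which are built from the extreme readings. If artifact-excluded readings count as missing, the same judgement could also decide who is analyzed.

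**Working it through.** **1. The blinding statements side by side**

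| Statement | Where | Compared with |
|---|---|---|
| Collection and analysis are by blinded investigators | Discussion | 2.9: unblinded anesthesiologists document T0–T43. Values at those points go into the CRF (2.10). |
| Investigators in patient care stay blinded at interim evaluations | 2.12 | 2.8 and 2.9: anesthesia providers know the arm. |
| The approach ensures unbiased collection and analysis | 2.9 | 2.6: readings are removed by inspection with clinical records. 2.9: drug rate is synchronized with MAP, and only anonymizing is described. |

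The first two rows conflict as written. In the third, the procedures described do not support the assurance.

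**2. Which analyses are touched**

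- T0–T43 feed the GEE analyses (2.6, 2.11). They would reach the ANCOVA only if T0 supplied baseline MAP or the marks set the observation window. Neither is stated.
- Artifact removal acts directly on TWA-MAP and both burdens.
- If removed readings count as missing, the 5% rule applies. In a 180-minute record (duration assumed), 5% is 9 minutes, and a tenth removed minute would take the participant out of the per-protocol set.

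**3. Planning difference, as a yardstick**

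From the quartiles in section 2.7, mean = (q1 + median + q3)/3 and SD = (q3 − q1)/1.35:

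- remimazolam: (76.9 + 81.3 + 92.5)/3 = 83.6; SD 15.6/1.35 = 11.6
- propofol: (67.8 + 76.8 + 82.5)/3 = 75.7; SD 14.7/1.35 = 10.9
- difference 7.87 mmHg, pooled SD 11.2, ratio 0.70, which reproduces the plan's effect size.

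**4. Upper bound on the shift**

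Assume normal, independent minute values with within-patient SD s = 10 mmHg, and that the lowest fraction f is deleted in one arm only. The shift in TWA-MAP is s·φ(z_f)/(1 − f). At f = 0.05: 10 × 0.1031/0.95 = 1.09 mmHg.

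For the hypotensive burden (MAP criterion only), take mean 75.7 and threshold 65, so k = (65 − 75.7)/10 = −1.07.

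- Mean depth below 65 per minute: 10·[φ(k) + k·Φ(k)] = 0.728 mmHg.
- Part lying in the deleted tail: 10·φ(z_f) − 10.7f. At f = 0.05 this is 1.031 − 0.535 = 0.496, and 0.496/0.728 = 68%.

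| Lowest minutes removed | TWA-MAP shift (mmHg) | Share of 7.87 | Fall in hypotensive burden |
|---|---|---|---|
| 1% | 0.27 | 3% | 22% |
| 2% | 0.49 | 6% | 37% |
| 5% | 1.09 | 14% | 68% |

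The shift is proportional to s. At 5% removal, s = 5 gives 0.54 mmHg and s = 15 gives 1.63 mmHg.

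**5. With autocorrelation and the plan's interpolation**

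Neighbouring minutes resemble each other, so interpolated values are also low. Simulated 180-minute first-order autoregressive traces (mean 75.7, SD 10; duration and correlation assumed), with the lowest 5% removed and then linearly interpolated, give:

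| Lag-1 correlation | TWA-MAP shift (mmHg) | Share of 7.87 | Fall in hypotensive burden |
|---|---|---|---|
| 0 | 1.07 | 14% | 66% |
| 0.8 | 0.43 | 5% | 49% |
| 0.9 | 0.32 | 4% | 36% |

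**The case against.** The strongest reply is that the protocol does name a blinded investigator as recipient of the trace data. What it hands over is called physiologic data, and section 2.10 speaks of extracting hemodynamic variables; neither phrase names drug channels. How the export is masked is an operational detail that an article may leave to the full protocol. This stands in part. A reader might infer that the artifact reviewer will see the drug, or that blinded assessment fails outright. The documents do not say so: masking is neither described nor excluded, and that the clinical records reveal the arm is a strong inference, not a stated fact. What remains is that the article gives an unqualified assurance, and the safeguard it describes does not by itself deliver it.

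A reader might also see a contradiction between inspection in section 2.6 and the predefined criteria in the Discussion. Predefined artifact classes can be identified by inspecting a waveform, so none is established. Nor would selective removal be untraceable, because section 2.10 archives the original recorder files and TWA-MAP could be recomputed.

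The time-point marks are mostly events or fixed clock intervals and mainly affect the GEE analyses, so they are no threat to the primary outcome as the text stands. The sentence in section 2.12 may be meant as blinding to interim findings, but it says group assignment.

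**Conclusion.** The point holds as an overstatement of blinding. The Discussion and section 2.12 claim blinding that sections 2.8 and 2.9 deny, and blinding of the artifact step is not supported by the procedures described. This does not show that bias will occur.

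The possible effect on TWA-MAP is small. With 5% of minutes removed in an arm-aware way it is at most about 1 mmHg under independent minutes and an assumed within-patient SD of 10 mmHg, roughly 14% of the planning difference. It falls to 0.3–0.4 mmHg with lag-1 correlations of 0.8–0.9 and the planned interpolation. The burdens are more exposed: in the same one-sided worst case the hypotensive burden falls by about 36% to 68%, depending on the correlation assumed. The route into the per-protocol set is conditional on artifact-excluded readings counting as missing, which the text neither states nor rules out.

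**What to change.** In sections 2.6 and 2.9, state that:

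- the blinded investigator carries out the artifact review, and completes it before unmasking;
- the files reviewed have the hypnotic infusion and effect-site channels removed;
- a drug-masked list of flush, zeroing and disconnection times replaces the full clinical records, with no drug or flumazenil entries;
- the number of minutes excluded is reported by arm.

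Correct section 2.9, section 2.12 and the Discussion to say that anesthesia providers and time-point marking are unblinded, and that only trace processing and analysis are masked. If section 2.12 means that care investigators do not see interim findings, it should say that instead.

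The cost is a small export step, preparation of the event list and some rewording. No extra staff or patients are needed, and patient care does not change.

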### Data management

2.10

All study data will be documented in standardized, paper-based CRFs developed for this trial. The CRFs will be pilot-tested in five patients before study initiation to ensure feasibility, clarity, and internal consistency. To maintain data quality, study personnel will receive pre-study training on CRF completion and data handling procedures. Duplicate checks of key variables (hemodynamic parameters and anesthetic drug doses) will be conducted, and 10% of completed CRFs will be randomly audited against source documents by an independent investigator. Any discrepancies will be resolved by consensus.

Intraoperative hemodynamic variables recorded using the Vital Recorder system will be extracted into a structured Excel file, which will serve as the source data. Relevant parameters, including MAP, HR, CO, CI, and SVV at each prespecified time point, will be transcribed into the CRF. The original Vital Recorder files will be archived as source documents linked to their corresponding CRFs.

To minimize missing data, participants will be observed continuously until discharge from the PACU. If a participant discontinues or deviates from the assigned intervention, outcome data will continue to be collected whenever feasible, including intraoperative hemodynamic variables, adverse events (hypotension, hypertension, bradycardia, and tachycardia), anesthetic drug doses, surgical characteristics, PACU duration, and postoperative vital signs. Reasons for non-adherence (e.g., conversion to inhalational anesthesia, conversion to open surgery, or discontinuation due to adverse events) and non-retention (withdrawal of consent or early termination) will be documented in the CRF. Participants who withdraw consent will be requested to permit use of data collected prior to withdrawal.

All data will be entered into a dedicated electronic database following completion of the paper CRFs. Double data entry will be conducted independently by two trained research personnel to minimize transcription errors. The database will incorporate predefined range and logic checks, and categorical variables will be coded according to a standardized data dictionary. The electronic database will be stored on a secure, password-protected institutional server with firewall protection and will be accessible only to the principal investigator and authorized study personnel. Paper CRFs and source documents will be stored in a locked cabinet within the research office. All study data will be retained for at least 3 years after publication in accordance with institutional policy and Good Clinical Practice requirements.

### Statistical analysis

2.11

The primary outcome, TWA-MAP, will be analyzed using analysis of covariance, with group assignment as the fixed factor and baseline MAP, age, BMI, ASA-PS, and histories of hypertension and diabetes as covariates. Secondary outcomes, including hypertensive and hypotensive burden (area under the curve above or below predefined thresholds), will be compared between groups using Student’s t-test for normally distributed variables or the Mann–Whitney U test for non-normally distributed variables. Categorical outcomes, such as intraoperative hypotension, hypertension, bradycardia, tachycardia, PONV, and postoperative analgesic use, will be evaluated using the chi-square test or Fisher’s exact test, as appropriate.

Repeated-measures variables across prespecified time points (T0–T43), including HR, SBP, DBP, MAP, CO, CI, SVV, ETCO_2_, and arterial blood gas parameters, will be analyzed using generalized estimating equations (GEE) to assess group, time, and group-by-time interaction effects. An appropriate working correlation structure will be selected to account for within-subject correlations over time. As a sensitivity analysis, GEE analysis of serial blood pressure data will be performed to evaluate consistency with findings from the primary TWA-MAP analysis.

The primary efficacy analysis will follow the per-protocol (PP) principle, including all randomized participants who fully adhere to the study protocol. Participants with major protocol deviations, such as conversion to open surgery, administration of inhalational anesthetics, incomplete intraoperative hemodynamic monitoring, or early withdrawal, will be excluded from the PP analysis. Participants who discontinue the intervention due to serious adverse events will also be excluded. No intention-to-treat analysis is planned. The safety population will include all participants who receive at least one dose of the assigned anesthetic agent and will be analyzed according to the treatment actually administered.

Missing data will be minimized through prospective monitoring of CRFs. For continuous outcomes, if ≤ 5% values are missing, linear interpolation will be performed; if > 5% are missing, the participant will be excluded from the PP analysis. For repeated-measures outcomes, non-parametric generalized estimating equations will accommodate incomplete time series, allowing valid population-level inference. For categorical variables, missing values will be reported explicitly, and sensitivity analyses will be conducted to evaluate their potential influence on study findings.

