As a sensitivity analysis, hemodynamic and respiratory parameters will be assessed at prespecified time points to evaluate temporal changes and validate consistency with the primary outcome. Measurements will be obtained before induction (T0); every minute for 10 min from induction drug initiation (T1–T10); every 10 min for 30 min after establishment of both the Trendelenburg position and pneumoperitoneum (T20–T23); at pneumoperitoneum release (T30) and 10 min afterward (T31); and upon PACU arrival (T40), followed by every 10 min for 30 min (T41–T43). Arterial blood gas analysis will be performed at T10, T21, and T31. During anesthesia induction and maintenance, HR, SBP, diastolic blood pressure (DBP), MAP, respiratory rate (RR), SpO_2_, ETCO_2_, cardiac output (CO), cardiac index (CI), and stroke volume variation (SVV) will be recorded. In the PACU, HR, SBP, DBP, MAP, RR, and SpO_2_ will be recorded at the same prespecified intervals.

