### Sample size

2.7

A previous study reported the median and interquartile range of intraoperative MAP during total intravenous anesthesia in patients receiving remimazolam or propofol (remimazolam: 81.3 [76.9–92.5] mmHg; propofol: 76.8 [67.8–82.5] mmHg) (Tsukimoto et al., 2024). Based on these findings, we will estimate the means and standard deviations using the method described by Wan et al. (2014). The required sample size was calculated using G*Power software (version 3.1; Heinrich Heine University, Düsseldorf, Germany). With 80% power and a two-sided significance level of 0.05, 26 participants per group are required (effect size = 0.7). To account for a 10% dropout rate, we will recruit a total of 58 patients.

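### The GEE models keep the pre-drug T0 value as an outcome point and name no baseline adjustment, which gives up precision in secondary and sensitivity analyses

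*Protocol article*

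**What the plan says.** Section 2.11 lists the GEE outcomes as "Repeated-measures variables across prespecified time points (T0–T43), including HR, SBP, DBP, MAP, CO, CI, SVV", followed by ETCO2 and blood gases, and says that these "will be analyzed using generalized estimating equations (GEE) to assess group, time, and group-by-time interaction effects". Section 2.6 fixes the timing: "Measurements will be obtained before induction (T0); every minute for 10 min from induction drug initiation (T1–T10". Section 2.8 adds that "the independent anesthesiologist will open the next envelope immediately before induction and disclose the allocation". T0 is therefore a pre-treatment value.

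The primary TWA-MAP model is handled differently. It is an ANCOVA "with group assignment as the fixed factor and baseline MAP, age, BMI, ASA-PS, and histories of hypertension and diabetes as covariates". For the GEE models the article names no baseline covariate and no constraint that the arms share a mean at T0. It leaves the within-patient structure open: "An appropriate working correlation structure will be selected to account for within-subject correlations over time".

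**The concern.** Under randomization the arms can differ at T0 only by chance. With T0 in the response, a group effect averaged over all times includes one point whose true effect is zero, and stable between-patient differences stay in the error. The group-by-time contrasts against T0 use it only as one end of a change score, which is less precise than conditioning on it.

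These models are the only between-group comparison of HR, CO and CI levels over time that the article states. For MAP they also serve as the sensitivity check on the primary result, which is itself baseline-adjusted. Section 3 concedes limited power for secondary outcomes, so precision available from data already collected is worth taking. What is at stake is power and a coefficient that could be misread.

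**Working it through.** **Inputs from the protocol.** Section 2.6 gives T0, T1–T10, T20–T23, T30–T31 and T40–T43, which is 1 + 10 + 4 + 2 + 4 = 21 points for HR, SBP, DBP and MAP. CO, CI and SVV are absent from the PACU list ("In the PACU, HR, SBP, DBP, MAP, RR, and SpO_2_ will be recorded at the same prespecified intervals"), which leaves 17. Section 2.7 gives 26 per arm and a two-sided 0.05 level.

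**The plan's own figure.** No power is stated for the GEE models. For the primary outcome the article states: "With 80% power and a two-sided significance level of 0.05, 26 participants per group are required (effect size = 0.7". A two-sided t-test at those values gives 0.697 (one-sided, 0.801). That is a separate matter. Here 70% is only a convenient starting level.

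**Step 1: dilution.** A constant effect from T1 onward, averaged over all points, shrinks to 20/21 = 95.2% with 21 points and to 16/17 = 94.1% with 17. The loss is about 5–6%.

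**Step 2: coding.** An exchangeable GEE with group × time was fitted to simulated data. With T0 as the reference time, the group coefficient equalled the raw T0 difference (−0.039 for both). With sum coding it equalled the average difference over all 21 times, T0 included (0.422). In this balanced saturated model the working correlation recovered no precision.

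**Step 3: precision.** Assumptions, none of them in the protocol: unit SD at each time, a constant post-induction effect δ, correlation r_w among the m post-T0 points, and correlation r_b between T0 and each of them. Per-patient variances are:

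- mean of the post-T0 points: V = (1 + (m − 1)r_w)/m
- planned average including T0: (m²V + 1 + 2m·r_b)/(m + 1)², with effect δ·m/(m + 1)
- post-T0 mean adjusted for T0: V − r_b²

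Example with m = 20, r_w = 0.5, r_b = 0.3:

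- V = (1 + 9.5)/20 = 0.525.
- Planned variance = (210 + 1 + 12)/441 = 0.506. Rescaled to the full effect, it is 223/400 = 0.5575.
- Adjusted variance = 0.525 − 0.09 = 0.435, and 0.435/0.5575 = 0.78, a 22% cut.

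δ is set in each case so that the planned effect has 70% power (noncentral t, 50 df; 49 df with the covariate). Power with T0 as a covariate, m = 20:

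| r_b | 0.1 | 0.2 | 0.3 | 0.4 | 0.5 |
|---|---|---|---|---|---|
| r_w = 0.5 | 71.8% | 75.1% | 80.3% | 87.2% | 94.9% |
| r_w = 0.7 | 71.3% | 73.8% | 77.5% | 82.7% | 89.1% |

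With m = 16 (CO, CI, SVV) the figures agree to within about half a point.

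**Step 4: simulation.** With 4,000 trials, 26 per arm, 21 times, all correlations 0.5 and a true effect of 0.50 SD, the planned effect averaged 0.480 with SE 0.200. With T0 as a covariate it averaged 0.503 with SE 0.148, about 26% smaller.

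**Step 5: change scores.** At one time point with correlation ρ, a change from T0 has variance 2(1 − ρ), and adjustment for T0 has 1 − ρ². At ρ = 0.3, 0.5 and 0.7 these are 1.40, 1.00 and 0.60 against 0.91, 0.75 and 0.51. Both are valid, and adjustment is the more precise.

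**Step 6: how the remedy is specified.** T0 plus T0-by-time adds 20 parameters to the 40 of group × time over 20 points. That makes 60 mean parameters for about 52 patients, and a trial fit gave a robust covariance matrix of rank 51. Constraining the arms to be equal at T0 is not automatically equivalent to a covariate. In one fit the constrained model under independence returned exactly the raw post-T0 difference (0.526), against 0.557 under exchangeable correlation and 0.563 by ANCOVA.

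**The case against.** The best defence is that one condensed sentence names effects to be tested and is not a full model specification. T0–T43 cannot be literal for every listed variable, since blood gases start at T10 and CO, CI and SVV stop before the PACU. An analysis plan could add baseline adjustment. That is fair as far as it goes, but the article does state which points form the series and which effects are assessed. T0 is a listed measurement time, and baseline adjustment is written out for the primary model only.

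The defence is stronger on weight. Keeping T0 in the response with group-by-time is a standard analysis. A reader might infer that chance T0 imbalance biases the comparison or inflates the type I error. The documents do not support that: the estimate is unbiased over randomization, and the imbalance is reflected in its standard error. The reference-coding problem depends on coding that the protocol does not state.

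A reader might also infer a large, assured power gain. The higher figures need T0 to correlate 0.4–0.5 with every later point. Titration of remifentanil, rescue drugs and the eligibility limits on SBP and HR could all weaken that correlation. The effect is also unlikely to be constant into the PACU, after the infusions have ended. At a T0 correlation of 0.1 the gain is only 1–2 points. Nor does the power of a single change contrast describe the planned multi-degree-of-freedom interaction test.

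**Conclusion.** The point holds as a modest loss of efficiency. For HR, SBP, DBP, MAP, CO, CI and SVV, the stated GEE models use a pre-drug value as an outcome and name no baseline adjustment. Dilution is about 5–6%. Starting from 70% power with 26 per arm, adjustment for T0 gives roughly 71–75% at T0 correlations of 0.1–0.2 and 78–95% at 0.3–0.5, with later points assumed to correlate 0.5–0.7 and the effect assumed constant. Blood gases have no T0 value and are not affected. The primary ANCOVA already adjusts for baseline MAP, so nothing here touches the primary result.

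**What to change.** In section 2.11, for each variable measured at T0:

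- Take T1 onward as the response, with group, time and group-by-time.
- Add the participant's own T0 value as a single covariate, with no T0-by-time term or only a phase-level one.
- Report the baseline-adjusted group difference over the post-induction points, for example by phase.

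If T0 is instead kept in the response with group means constrained equal there, specify a non-independence working correlation, such as exchangeable. Under independence the constraint gains no precision.

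The cost is one or two sentences before unblinding, one extra parameter per model, and the loss of any patient with a missing T0 value. T0 is already collected, so no new data or patients are needed.
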